### 4. Diagnostic criteria and disease stage / type classification

The diagnostic criteria and disease stage/type classification (definition) of the disease or condition specified in the eligibility criteria of this study are shown below.

Definition of chronic kidney disease

Defined as (i), (ii), or both are sustained for over three months.

(i) Renal damage revealed by abnormal urine, diagnostic imaging, blood, and pathology.

Proteinuria of over 0.15 g/gCr (albuminuria of over 30 mg/gCr) is particularly important

(ii)  $\text{GFR} < 60 \text{ mL/min/1.73 m}^2$

Calculation equation of estimated GFR (eGFR)

The estimated GFR (eGFR) is calculated using the following serum creatinine estimation equation (eGFRcreat):

$$\text{Male eGFR}_{\text{creat}}(\text{mL/min/1.73 m}^2) = 194 \times \text{Cr}^{-1.094} \times \text{age}^{-0.287}$$

$$\text{Female eGFR}_{\text{creat}}(\text{mL/min/1.73 m}^2) = 194 \times \text{Cr}^{-1.094} \times \text{age}^{-0.287} \times 0.739$$

Definition of renal anemia

1) Renal anemia is defined as anemia caused by a decrease in EPO production ability in the kidney due to renal damage.

2) Renal anemia includes a shortened red blood cell lifespan, decreased EPO response of hematopoietic cells, malnutrition, and in-circuit residual blood in HD patients.

## 5. Eligibility criteria

Patients with chronic kidney disease and renal anemia who satisfy all the following selection criteria at the time of registration and for whom none of the exclusion criteria apply.

### 5.1 Selection criteria

- 1) Patients who are scheduled to start treatment with darbepoetin alfa within eight weeks after registration and who have not received ESA within 12 weeks prior to registration
- 2) Patients with an eGFR less than 60 mL/min/1.73 m^2 at the latest inspection within eight weeks prior to registration
- 3) Patients with an Hb concentration less than 11.0 g/dL at the latest inspection within eight weeks prior to registration
- 4) Patients aged over 20 years at the time of consent acquisition
- 5) Patients who voluntarily provide written consent regarding participation in this research

### 5.2 Exclusion criteria

- 1) Patients who plan to initiate maintenance dialysis or have a kidney transplant within 24 weeks after registration
- 2) Patients with malignant tumors, blood disorders, or obvious hemorrhagic lesions
- 3) Patients with hypersensitivity to ESA components or to ESA
- 4) Pregnant women, lactating women, patients who may be pregnant, or patients wishing to become pregnant during the research period
- 5) Patients participating in other clinical trials
- 6) Other patients deemed inappropriate for this research by the lead principal physician or study physician

## 6. Explanation and consent

The lead principal physician or study physician will sufficiently explain the research content to patients thought to be appropriate as subjects of this research based on explanations/consent documents set at each facility prior to participating in this research. Research collaborators can provide supplementary explanations for this research at this time. After giving patients sufficient time to consider whether to participate in the study, the lead principal physician or study physician will obtain the patient's voluntary consent to participate in the research in writing.

The lead principal physician or study physician who provided the explanation as well as the patient will write their name and provide their seal on the consent document or sign it, and each individual will write the date. Research collaborators who provide supplementary explanations will do the same.

If the individual cannot sign due to difficulties in writing, verbal consent will be obtained by the individual, and their representative will provide written consent. At that time, the date on which the

representative provided written consent, relationship with the patient, reason for consent by the representative (e.g., difficulties in writing), and date on which the patient provided verbal consent will be recorded on the consent document.

The lead principal physician or study physician will provide a copy of the consent form for the patient's records as well as an explanatory document to the patient. The lead principal physician or study physician will also store the consent documents for research in the medical institution's records along with the treatment records.

When there are issues relating to the decision to continue participation in this research, the lead principal physician or study physician will revise the explanatory document, provide explanations to patients participating in the research using the revised explanatory document, and obtain voluntary written consent from the individual regarding the continuation of participation in this research.

If possible, a withdrawal letter is created when a patient participating in the research submits a withdrawal of consent. The patient will write their name and provide their seal or sign as well as write the date of consent withdrawal, and the lead principal physician or study physician will write their name and provide their seal or sign the confirmation date. The lead principal physician or study physician will provide a copy of the signed and sealed consent withdrawal form to the patient, and the original consent withdrawal form will be stored at the applicable medical institution.

## **7. Research participation procedure and patient registration**

### **7.1 Research participation procedure**

A central registration system at the TRI data center in the Translational Research Informatics Center (henceforth, "data center") will be used to register for participation in this research. Facility registration and participating physician registration will be conducted using the following procedure.

#### **7.1.1 Facility registration**

- 1) The lead principal physician will send a copy of the affiliated facility ethics review board (Note) approval notification form to the BRIGHTEN TRI secretariat in the Translational Research Informatics Center by FAX.

Note: Another committee is acceptable if they are a committee that would examine the scientific validity, ethical validity, etc. of this research.

- 2) The BRIGHTEN TRI secretariat will submit the information of the facilities judged to be able to participate based on the obtained materials to the data center.
- 3) The data center will conduct facility registration and send a facility registration completion notification form to the lead principal physician.
- 4) The lead principal physician will confirm the eClinical Base website URL and initial password\* for user account authentication described in the facility registration completion notification form.

\*Initial password for user account authentication: temporary password used when setting the user

ID and password.

#### 7.1.2 User registration

- 1) The lead principal physician or study physician will access the eClinical Base website URL recorded on the facility registration completion notification form, enter the necessary information on the website, and apply it to the user.
- 2) After applying for the user, the lead principal physician or study physician will print out the self-signed confirmation form, sign it, and send this to the data center by FAX.
- 3) The data center will e-mail a “temporary user account URL” for setting the user ID and password to the lead principal physician or study physician who applied for the user.
- 4) The lead principal physician or study physician will set a user ID and password online.

User registration is conducted using the same procedure under the supervision of the lead principal physician when the research collaborators input case report form data.

#### 7.2 Patient registration

A central registration system at the data center is used for patient registration. Patient registration is conducted using the following procedure:

- 1) The lead principal physician or study physician will conduct the necessary inspections for determining the eligibility of patients whose participation in this research is deemed possible.
- 2) The lead principal physician or study physician will access the eClinical Base website URL and input patient information on the website. The patient identification code used at this time will not include individual information at each facility, and a unique and arbitrary code is used.
- 3) Observations according to protocol will be implemented when deemed eligible according to eligibility criteria.
- 4) An “anonymization number comparison table,” etc. will be created at each facility to ensure that there is no misidentification of patients, and the lead principal physician of each facility or a representative will appropriately store and manage the anonymization number comparison table.
- 5) The lead principal physician or study physician will input case report form data on the website after patient registration. However, research collaborators can input this under the supervision of a lead principal physician.
- 6) The input and input deadline of the case report form will follow the “Input and submission of case report form.” Questions regarding the input method should be directed to the data center.

## 8. Treatment plan

[figure not shown]

### 8.1 Recommended renal anemia treatment

This research is an observational study, so the following treatment methods are recommended.

Among CKD patients diagnosed with renal anemia, those for whom ESA administration was deemed necessary will receive the expected DA according to the package insert and observed for 96 weeks from the start of treatment (see Section 8.1.1 for target values of renal anemia treatment).

The participants in this study will include patients who did not receive ESA within 12 weeks prior to registration, and inspections in this research will be implemented following consent acquisition. DA administration will begin within eight weeks after registration.

The final administration of DA during the observation period will be performed immediately before 96 weeks after the start of treatment, but treatment will be continued as necessary after the completion of the observation period.

#### 8.1.1 Target values of renal anemia treatment

Refer to the latest information, such as the guidelines of academic societies, etc., for the target Hb concentration in ESA therapy.

#### 8.1.2 Recommended darbepoetin alfa administration method

The following administration method is recommended for darbepoetin alfa according to the guidelines and latest package inserts.

**Table Target Hb concentrations of each guideline and the Hb concentration at the start of treatment**

| Guideline                 | Target Hb concentration                                               | Hb concentration at the start of treatment |
|---------------------------|-----------------------------------------------------------------------|--------------------------------------------|
| 2008 Japanese Society for | Over 11 g/dL. Consider dose reduction / suspension if over 13 g/dL*1. | Less than 11 g/dL                          |

| Dialysis Therapy                  |                                                                         |                                 |
|-----------------------------------|-------------------------------------------------------------------------|---------------------------------|
| 2012
CKD clinical
guideline | 10-12 g/dL. Take measures not to exceed 12 g/dL. Do not exceed 13 g/dL. | Less than 10 g/dL               |
| 2012
KDIGO guideline           | 10-11.5 g/dL *2 . Do not exceed 13 g/dL.                     | Less than 10 g/dL *3 |

\* 1 However, consider dose reduction/suspension for patients already with or who have complications of serious CVD or those with medical needs when the Hb concentration exceeds 12 g/dL.

\* 2 Quality of life (QoL) may improve in certain patient groups even when the Hb concentration exceeds 11.5 g/dL and makes the risk acceptable, so it is thought that treatment according to each individual patient is needed.

\* 3 QoL may improve in certain patient groups at even higher Hb concentrations, and ESA therapy may start at a stage of >10 g/dL, so treatment according to each individual patient is valid.

(Reference: "Evidence-based CKD practice guideline 2013")

(refer to the package insert, 2008 edition of the "Guidelines for the treatment of renal anemia in patients with chronic kidney disease" by the Japanese Society for Dialysis Therapy)

The package insert (excerpt) is shown below.

#### 【Dosage and administration】

- Initial dose

Adult: A usual adult dose of 30 µg of darbepoetin alfa (genetic recombination) per session is administered subcutaneously or intravenously once every two weeks.

- Maintenance dose

Adult: When improved effects are seen for anemia, a usual adult dose of 30–120 µg of darbepoetin alfa (genetic recombination) per session is administered subcutaneously or intravenously once every two weeks. When anemia improvement is maintained with an administration once every two weeks, then the starting dose is twice the dose at that time; dosing frequency is changed to once every four weeks, and 60–180 µg per session can be administered subcutaneously or intravenously once every four weeks.

The dose may be adjusted according to the extent of anemic symptoms, age, etc., but the maximum administered dose is set at 180 µg per session.

#### 【Dose adjustment】

The dose should be adjusted with reference to Table 8.2-1 in cases where dose adjustments are necessary, such as when appropriate increases in the Hb concentration or hematocrit value are not observed in the initial administration period, or when the Hb concentration or hematocrit

value deviated from the target range for two consecutive weeks during the maintenance administration period. When increasing doses, do so one step at a time as a general rule.

The table below shows the dose adjustment table for subcutaneous administration. The latest package insert for intravenous injections was followed.

**Table 8.2-1 Dose adjustment table for adults (during subcutaneous administration)**

| Step | Administered dose of this drug |
|------|--------------------------------|
| 1    | 15 µg                          |
| 2    | 30 µg                          |
| 3    | 60 µg                          |
| 4    | 90 µg                          |
| 5    | 120 µg                         |
| 6    | 180 µg                         |

**【When changing administration level】**

- 1) When changing the administration interval of this drug, shifts in the Hb concentration or hematocrit value will be sufficiently observed prior to extending the administration interval to confirm that stable shifts in the Hb concentration or hematocrit value are shown at the same administered dose. After doing so, change from once a week to once every two weeks, or once every two weeks to once every four weeks. Confirm shifts in the Hb concentration or hematocrit value after the change and adjust as appropriate.
- 2) Patients in whom the Hb concentration or hematocrit value did not reach the target range even after administering 180 µg per session should change the administered dose to 1/2 and change the administration frequency from once every two weeks to once every week, or once every four weeks to once every two weeks.

## 8.2 Discontinuation criteria for each patient and its handling

The necessary items are recorded up to the traceable time point in the case report form and the “discontinuation report form” in the following patients.

- 1) When a patient has died.
- 2) When a patient cannot be contacted and becomes untraceable.

However, if the transfer destination is known, the patient will be tracked by obtaining data from the transfer destination facility or by calling, and tracing will be continued.

- 3) When a patient requests discontinuation from research participation (patient information prior to discontinuation can be used).
- 4) When a patient has requested consent withdrawal (patient information after registration cannot be used).

- 5) When the lead principal physician or study physician deemed that research participation should be discontinued.

Patients in whom any of the following are applicable are not considered discontinued, with normal observation period inspections continued to the extent possible, and information up to the time point of 96 weeks collected.

- 1) Patients who transitioned to renal replacement therapy (dialysis, kidney transplantation).
- 2) When a patient has requested discontinuation of darbepoetin alfa use.
- 3) When the lead principal physician or study physician deemed that darbepoetin alfa use should be discontinued due to adverse events, etc.

The lead principal physician or study physician will make efforts to provide the best possible treatment to the patient even after discontinuation of research participation.

If it was determined after registration that a patient did not meet the eligibility criteria at the time of registration, then this will be considered “ineligible after registration,” and research participation will be concluded for the patient. Adverse event information up to 30 days after the decision to complete participation will be reported for patients in whom darbepoetin alfa was administered even once.

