#### 10.1.4 Simultaneous outcome survey (96 weeks from the start of the final registered patient)

A simultaneous outcome survey will be conducted for all patients 96 weeks after the start of the final registered patient.

|        |                                                   |                                            |                                                                                                                                            |                                                                                                                                                                                                                                                                                                                                                                                                                                |
|--------|---------------------------------------------------|--------------------------------------------|--------------------------------------------------------------------------------------------------------------------------------------------|--------------------------------------------------------------------------------------------------------------------------------------------------------------------------------------------------------------------------------------------------------------------------------------------------------------------------------------------------------------------------------------------------------------------------------|
| 1      | Outcome                                           | Outcome status                             | Survival
Death (cause of death: fatal CVD event, other (details))
Unknown (reason)                                                   |                                                                                                                                                                                                                                                                                                                                                                                                                                |

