#### 10.1.5 When discontinuing / withdrawing consent for participation in research

Provide answers within four weeks of discontinuation or consent withdrawal from research participation. Items from two onwards are not needed for patients who withdraw consent. Investigations during the normal observation period are continued if the patient can be traced even after the discontinuation of darbepoetin alfa administration or after event occurrence.

|    |                                                             |                                           |                                                                                                                                            |                                                                                                                                                                                                                                                                                                                                                                                                                                |
|----|-------------------------------------------------------------|-------------------------------------------|--------------------------------------------------------------------------------------------------------------------------------------------|--------------------------------------------------------------------------------------------------------------------------------------------------------------------------------------------------------------------------------------------------------------------------------------------------------------------------------------------------------------------------------------------------------------------------------|
| 1  | Research participation discontinuation / consent withdrawal | Discontinuation / consent withdrawal date | yyyy/mm/dd                                                                                                                                 |                                                                                                                                                                                                                                                                                                                                                                                                                                |

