|    |                                                             | Onset date                                | yyyy/mm/dd (date of initial diagnosis when unknown)                                                                                        |                                                                                                                                                                                                                                                                                                                                                                                                                                |

|    |               |                                           |                                                                               |
|----|---------------|-------------------------------------------|-------------------------------------------------------------------------------|
| 5* | Adverse event | Event name                                | [Written accordingly]                                                         |
|    |               | Occurrence date                           | yyyy/mm/dd                                                                    |
|    |               | Severity                                  | Severe, not severe (refer to 9.1.2 Definition of serious adverse events)      |
|    |               | Causal relationship with darbepoetin alfa | Present, absent                                                               |
|    |               | Outcome                                   | Recovery, remission, non-recovery, recovery but with sequelae, death, unknown |
|    |               | Outcome confirmation date                 | yyyy/mm/dd                                                                    |

Provide the status from the previous survey point to the survey point at the time of discontinuation/consent withdrawal.

\*1: New-onset (asymptomatic) myocardial infarction is treated as an event, even without hospitalization.

\*2: Includes old myocardial infarction, valvular disease, epicarditis, etc.

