#### 11. Sample size and research period

##### 11.1 Sample size

The sample size is 2,000 patients.

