### 13. Statistical analysis

#### 13.1 Rationale for the sample size design

The objective of this research is to clarify the actual conditions of low ESA response cases in Japan, investigate factors related to low ESA response cases, and search for new ERIs. Therefore, in consideration of securing data for each type of exploratory analysis, a sample size of 2,000 was set as the scale of research where evaluations of low ESA response cases were thought to be possible.

The TREAT trial conducted internationally reported that renal events (end-stage renal failure or death) in the darbepoetin alfa group and the two-year occurrence rate of CVD events was approximately 23%–24%. If the event occurrence rate was set as 13.1 / 100 people/year from this result, then the number of events observed in two years with a sample size of 2,000 would be 480–568 patients at a 95% confidence interval, which is thought to be a sufficient number of events for the planned analyses.

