## 13.3 Analysis items / methods

As a general rule, categorical data calculate frequencies and percentages, and continuous values are summarized with the summary statistical values of the number of patients, average value, standard deviation, minimum value, median value, and maximum value.

A significance level is not set because there are no hypotheses to be verified that are set in this research, but a two-sided P-value of 5% is set when using statistical test methods in an exploratory manner.

Details on analyses not recorded in this research protocol are described in the “Statistical Analysis Plan”

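### A physician may end participation for any reason (Protocol 8.2, item 5), and the protocol does not secure outcome follow-up for such a patient, even one who is traceable and has not asked to stop

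*Protocol*

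**What the plan says.** Section 8.2 sorts patients into two lists.

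- **Discontinued:** death, loss of contact, patient request, withdrawal of consent and, as item 5, "When the lead principal physician or study physician deemed that research participation should be discontinued". The sentence opening this list has the necessary items recorded for as far as the patient can be traced.
- **Not treated as discontinued:** patients who move to dialysis or transplantation, and those whose darbepoetin is stopped at their own or the physician's decision. Only this list carries a promise of information to week 96.

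Section 10.1.5 describes the form completed at discontinuation and gives physician decision as a reason of its own. Its reporting window is: "Provide the status from the previous survey point to the survey point at the time of discontinuation/consent withdrawal". The same section says that normal investigations are "continued if the patient can be traced even after the discontinuation of darbepoetin alfa administration" or after an event. It does not mention the end of participation.

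Section 10.1.4 states: "A simultaneous outcome survey will be conducted for all patients 96 weeks after the start of the final registered patient". That survey collects vital status, CVD events and renal events since the previous survey point.

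**The concern.** Item 5 is the only ground in the first list that can remove a patient who is alive, traceable and has asked for nothing. The person deciding knows the haemoglobin, the dose and the clinical course. Haemoglobin and dose are also what the response indices in 12.3 are built from.

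Both primary endpoints (12.1.1 and 12.1.2) are times to event from week 12. The Kaplan-Meier, proportional hazards and time-dependent ROC analyses in 13.3.1 rely, in their usual form, on censoring that is unrelated to prognosis given what the model contains. If outcome recording stops at a physician's decision, and that decision follows the patient's course, the assumption fails. If such exits are also commoner among poor responders, the events lost come mainly from the group of interest. An analysis plan can describe this, but it cannot restore data that were never collected.

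**Working it through.** **1. The passages side by side**

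| Place | Bearing on a traceable item 5 patient |
|---|---|
| 8.2, opening sentence | Recording as far as tracing allows. It also covers deaths and withdrawals of consent, so it is not a clear promise of later follow-up |
| 8.2, second list | Week 96 collection, but for other patients |
| 10.1.5, continued investigation | Named for stopping the drug and for events only |
| 10.1.5, form window | Closes at discontinuation |
| 10.1.4 | Survey of all patients. This cannot be fully literal, since 8.2 bars use of post-registration data after consent is withdrawn |

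No passage says whether an item 5 patient stays in the survey. Even if so, two renal components in 10.4.1 (the 50% fall in eGFR and eGFR of 6 or below) need three consecutive points. One survey at the end may not establish them if scheduled measurements have stopped.

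**2. The plan's own event count (13.1)**

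Inputs: "The sample size is 2,000 patients" and "If the event occurrence rate was set as 13.1 / 100 people/year from this result". Expected events = 2,000 × 2 × 0.131 = 524. The Poisson interval is 524 ± 1.96 × √524 = 479.1 to 568.9. This reproduces the protocol's statement that "the number of events observed in two years with a sample size of 2,000 would be 480–568 patients at a 95% confidence interval". The present point does not change that figure.

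**3. Events at stake (illustration)**

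From the protocol: 2,000 patients, a rate r of 0.131 per year, and weeks 12 to 96, so T = 84 × 7 / 365.25 = 1.610 years. Assumed: a share d of patients is stopped under item 5, at times u spread evenly over T; the hazard afterwards is k times r; nothing is recorded after the stop.

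- Unrecorded events = 2,000 × d × mean over u of exp(−ru) × [1 − exp(−kr(T − u))]. For d = 5% and k = 3 the mean is 0.241, giving 2,000 × 0.05 × 0.241 = 24.
- Kaplan-Meier risk with censoring at the stop = 1 − exp(−0.131 × 1.610) = 19.0% in every cell.
- True risk = (1 − d) × 19.0% + d × mean over u of [1 − exp(−ru − kr(T − u))].

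| d | k = 1: events lost, true risk | k = 2 | k = 3 |
|---|---|---|---|
| 2% | 4, 19.0% | 7, 19.2% | 10, 19.3% |
| 5% | 9, 19.0% | 17, 19.4% | 24, 19.8% |
| 10% | 18, 19.0% | 34, 19.8% | 48, 20.5% |

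At k = 1 events are lost but the risk is not biased.

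**4. Contrast between response groups (illustration)**

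All inputs except T are assumed: 12 events per 100 patient-years in the low-index group, rate ratio 1.5, and 25% of patients in the high-index group. The overall rate is 12 × (0.75 + 0.25 × 1.5) = 13.5, close to the protocol's 13.1. Rate = events / person-time in each group. With censoring at exit the rate is the group's own r, so the ratio is 1.50 by construction. Full follow-up adds the post-exit events of step 3 and person-time equal to those events divided by kr.

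| Exits, low / high index | k | Events lost | Ratio, full follow-up | Ratio, censored |
|---|---|---|---|---|
| 1% / 2% | 2 | 1.2% | 1.51 | 1.50 |
| 2% / 5% | 2 | 2.6% | 1.52 | 1.50 |
| 3% / 10% | 3 | 6.2% | 1.58 | 1.50 |
| 5% / 15% | 3 | 9.5% | 1.61 | 1.50 |
| 5% / 5% | 3 | 6.0% | 1.50 | 1.50 |

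The contrast shrinks only when exits are both prognostic and unequal between the groups.

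**The case against.** A reader might infer that a physician's decision ends event recording outright. The documents do not say so. The opening of 8.2 ties recording to traceability for all five grounds. Items 3 and 4 carry explicit limits on data use and item 5 carries none. The survey window in 10.1.4 starts at the previous survey point, so on a literal reading it resumes where the discontinuation form ends. That part of the objection stands: this is an unresolved conflict, not a stated rule.

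It also stands that the most obvious informative routes are closed. Patients who start renal replacement or stop darbepoetin are kept, and transferred patients are traced. Item 5 is what remains, and nothing links it to response or prognosis. Nor do the documents support a claim that the study's results will be biased towards no difference, because the shrinkage in step 4 comes from the assumed exit rates and hazards.

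Finally, the study sets no hypothesis, and "a two-sided P-value of 5% is set when using statistical test methods in an exploratory manner". That lowers the stakes but does not remove the point. The search for an index rests on these events, and the conflict concerns what is collected, which no later analysis choice can repair.

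**Conclusion.** The point holds as a gap in securing follow-up. The ground is unrestricted, week 96 collection is promised only to other patients, and the passages conflict on whether item 5 patients are still followed. The likely working reading at sites is that follow-up ends, but that is an inference, and sites may settle it differently.

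The size cannot be derived from the document. Under the assumptions shown, it runs from about 4 to 48 unrecorded events and from no bias to 1.5 percentage points of 84-week risk. The rate ratio is unchanged with equal exits and falls from 1.61 to 1.50 in the most unequal case. The effect is negligible if exits are rare, and no bias arises if they are unrelated to prognosis. The change is worth making because it is cheap and bears on both primary endpoints.

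**What to change.** Reconcile 8.2, 10.1.4 and 10.1.5:

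- **8.2:** state that under item 5 the physician may end study-specific procedures, but that a patient who has neither requested discontinuation nor withdrawn consent stays under outcome follow-up to week 96. This covers vital status, dialysis or transplantation, CVD events and routinely available eGFR. The separate rule for patients found ineligible after registration need not change.
- **10.1.4:** state that the simultaneous outcome survey includes these patients.
- **10.1.5:** add the end of participation by physician decision to the situations in which investigation continues while the patient can be traced, so that the discontinuation form is not the last record of events.

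The cost is a few sentences and a small extra reporting workload at sites. Including routine eGFR lets the renal components that need three consecutive points still be assessed where measurements exist, without extra study visits.
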